### Eligibility criteria

Inclusion criteria: (1) Aged between 1 and 6 years; (2) American Society of Anesthesiologists (ASA) physical status of II or III; (3) body mass index (BMI) between 14 and 18 kg/m^2^; (4) scheduled for FFB under general anesthesia due to conditions such as pneumonia, broncho-alveolar lavage (BAL), airway mucosal biopsy, or foreign body removal.

Exclusion criteria: (1) pulse oxygen saturation (SpO_2_) < 90% before FFB; (2) preoperative acute exacerbations of cough which is specifically defined as a clear increase in cough frequency to approximately twice that of the patient’s typical baseline pattern during the current illness, as reported by the parent/guardian, and this increase is not a feature of the child’s illness in the preceding days. This assessment will be guided by using a simple categorical scale: “Is your child coughing noticeably more often today than they were 2 days ago? Would you estimate it as “a little more,” “about twice as much,” or “much more than twice as much?”” A report consistent with “about twice as much” or “much more than twice as much” will meet this criterion; (3) history of allergy to relevant medications; (4) contraindications for the use of muscle relaxants such as mediastinal tumors; (5) hypertrophy of the tonsils and adenoids that may potentially affect the proper placement of the laryngeal mask; (6) second- or third-degree heart block; (7) history of asthma.

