### Randomization and blinding

An independent biostatistician, not involved in data management or analysis, generates the randomization list using a validated online tool^1^. The randomization is carried out using a 1:1 allocation ratio and permuted blocks of sizes 2 and 4. The allocation sequence will be executed using a password-protected, web-based randomization module. The encrypted database can be accessed only by an unblinded trial nurse. Based on the randomization list, the nurse will prepare and distribute the study medications (rocuronium or normal saline placebo) in identically labeled syringes marked only with study numbers. It is visually impossible to distinguish the contents of these syringes because both rocuronium and normal saline are clear and colorless solutions. Patients, endoscopists, outcome observers, researchers responsible for recording the data, and data analysts will all be kept blinded to the group assignment until the final analysis is finished. Due to safety considerations and the necessity of monitoring the train-of-four (TOF) ratio, the primary anesthetist, responsible for administering anesthesia to the patients as well as monitoring the TOF ratio at the ulnar nerve, is unblinded to the group assignments. However, the primary anesthetist neither knows the hypothesis of this study nor participates in outcome assessment. The patient recruitment, study interventions, and outcome measurement schedule are presented in Table 1.

**TABLE 1 T1:** Schedule of patient enrollment, study intervention, and endpoint measurement.

Timepoint	Study period				
	Enrollment	Allocation	Post-allocation		
	Preanesthetic visit	Before operation	During operation	PACU	24 h after the operation
Enrollment	×	×			
Inclusion criteria	×				
Exclusion criteria	×				
Written informed consent	×				
Baseline characteristics	×				
Preoperative cough status	×				
Randomization					
Allocation		×			
Intervention					
Group rocuronium			×		
Group normal saline			×		
Endpoint measures					
Frequency of coughing episodes			×	×	×
Cumulative remifentanil dosage			×		
Failure rate			×		
Hemodynamic variables			×		
Cough scores in the PACU			×		
Procedure time				×	
Discharge time			×		
Adverse events				×	
Satisfaction scores of bronchoscopist			×	×	
Satisfaction scores of anesthesiologist					
Satisfaction scores of parents					

According to SPIRIT 2013 statement of defining standard protocol items for clinical trials. PACU, post-anesthesia care unit.

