
#### During the procedure

An Olympus BF-XP290 flexible fiberoptic bronchoscope with an outer diameter of 2.8 mm, or a BF-P290 with an outer diameter of 4.0 mm is inserted through the bronchoscope connector. The suction port is sealed with a Polyvinyl Chloride cover to create an airtight seal around the bronchoscope. When the vocal cords are visualized, 2% lidocaine, usually administered in a volume of 1 mL, is applied to the vocal cords via the bronchoscope to prevent laryngospasm. Then, the vocal cords are carefully traversed, and 1 ml of 2% lidocaine is instilled into the tracheobronchial tree using the “spray as you go” technique (27). Further diagnosis and treatment of the airway using a flexible bronchoscope is performed based on the specific clinical context. The infusion rate of remifentanil is adjusted every minute, increasing or decreasing by 0.01 μg⋅kg^–1^⋅min^–1^ based on any signs of coughing. If a cough reaction occurs, the infusion rate is increased; if no cough reaction is observed, the infusion rate is decreased, as determined by the primary anesthesiologist. Supplemental boluses of 1–2 μg⋅kg^–1^ remifentanil will be administered as a remedy and repeated as needed in the event of persistent coughing. If blood pressure or other hemodynamic parameters preclude the administration of adequate doses of remifentanil, a supplementary dose of rocuronium (0.2 mg⋅kg^–1^) is administered. Cases in which a supplementary dose of rocuronium is administered are defined as those “with the highest incidence of coughing” and are categorized as “failure cases.”

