#### Sample size

In a previous study by Tschiedel et al. comparing the use of propofol alone versus propofol combined with remifentanil during FFB, the addition of remifentanil resulted in a reduction of coughing episodes by approximately 60%, from 1.98 to 0.73 episodes per minute (1). Before implementing this trial, we prospectively studied 20 children undergoing FFB from April 2025 to May 2025. Our findings revealed that the frequency of cough episodes in children using the propofol-remifentanil regimen ranged from 0.6 to 0.89 episodes per minute, with a standard deviation (SD) of 0.3 episodes per minute, which is consistent with previously published data. Another 50% reduction in coughing episodes, decreasing the frequency to 0.3 episodes per minute with rocuronium, represents not only a statistically significant difference but also a clinically relevant improvement. We will require 64 subjects per group to achieve a power of 0.80 with a type I error rate of 0.05. Accounting for an anticipated dropout rate of 10%, the adjusted estimated sample size will be 70 children per group, resulting in a total of 140 children being randomized.

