#### Statistical analysis

All data will be checked for normal distribution using the Kolmogorov test. For normally distributed data, continuous variables will be presented as mean ± SD and analyzed using the independent Student’s *t*-test. Nonnormally distributed data will be presented as the median and interquartile range (IQR) and compared using the Mann-Whitney U test where appropriate. Categorical data are presented as numbers (proportions, %) and will be analyzed using Fisher’s exact test or the chi-square test. For the study endpoints, 95% confidence intervals will be reported as appropriate to provide a more comprehensive understanding of the results.

The primary endpoint is the frequency of coughing episodes during the FFB operation period. If the primary endpoint adheres to a Poisson distribution or a negative binomial distribution, negative binomial regression is further utilized, adjusting for the influence of covariates [the severity classification of pneumonia, BMI, age, sex and operation time, baseline cough frequency (“occasional” or “frequent but stable”)]. If the primary endpoint conforms to a normal distribution, a multiple linear regression model is further adopted for the same covariate adjustment. Subgroup analyses for the primary endpoint will be performed according to age (<3 years old vs. ≥3 years old), sex (female vs. male), BMI (<15 vs. ≥15), operation type (BAL vs. BAL + airway mucosal biopsy vs. foreign body removal) and operation time (<20 min vs. ≥20 min). Recognizing the possibility of intra-observer variability in applying the cough threshold, we conducted a pre-specified sensitivity analysis for the primary endpoint. The frequency of coughing episodes will be re-calculated using two alternative, stricter definitions: “Worst-case” consolidation and “Best-case” granularity. The conclusions of the primary analysis are considered robust only if the between-group difference (rocuronium vs. normal saline) remained statistically significant (*p* < 0.05) in the same direction under both alternative sensitivity analysis scenarios.

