The secondary endpoints will be analyzed using the multivariate logistic regression model or the generalized linear model, adjusting for the same covariates as those of the primary endpoint. Repeated measurement data will be analyzed using a mixed linear model to compare haemodynamic variables and cough scores in the PACU between groups. To address the issue of multiple comparisons for adverse events observed in secondary endpoints, the Benjamini-Hochberg procedure will be employed to control the false discovery rate.

The analysis will be performed on the modified intention-to-treat population. To ensure robustness, a per-protocol analysis will additionally be conducted; however, the intention-to-treat approach will remain the primary basis for analysis. Missing data will be processed by multiple imputation and maximum likelihood method. All endpoints are performed at the two-sided 5% significance level. Statistical analyses will be performed using SPSS statistics (version 19.0; IBM SPSS, Chicago, IL, USA).

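### Operation type is a subgroup factor but not a covariate: adding the type scheduled before randomisation would gain some precision at almost no cost

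*Protocol article*

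**What the plan says.** All references are to the protocol article.

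- **Primary model (Statistical analysis).** Negative binomial or multiple linear regression, "adjusting for the influence of covariates [the severity classification of pneumonia, BMI, age, sex and operation time, baseline cough frequency". Operation type is not among these six covariates.
- **Subgroups (same section).** Operation type is one of the subgroup factors for the primary endpoint, at three levels: "operation type (BAL vs. BAL + airway mucosal biopsy vs. foreign body removal".
- **Secondary models (same section).** Logistic or generalized linear models, "adjusting for the same covariates as those of the primary endpoint". A separate sentence covers haemodynamics and PACU cough scores and names no covariates: "Repeated measurement data will be analyzed using a mixed linear model to compare haemodynamic variables and cough scores in the PACU between groups".
- **Eligibility criteria.** Children are "scheduled for FFB under general anesthesia due to conditions such as pneumonia, broncho-alveolar lavage (BAL), airway mucosal biopsy, or foreign body removal", so the reason for the procedure is known before allocation.
- **Randomization and blinding.** "The randomization is carried out using a 1:1 allocation ratio and permuted blocks of sizes 2 and 4"; no stratification factor is stated.
- **During the procedure.** "Further diagnosis and treatment of the airway using a flexible bronchoscope is performed based on the specific clinical context".
- **Discussion, limitations.** Airway inflammation and irritability from pneumonia or a foreign body is acknowledged as a possible confounder. The stated response is to record baseline cough frequency and adjust for it.

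**The concern.** The plan adjusts for sex and for BMI, which eligibility already confines to 14 to 18 kg/m², but not for what is going to be done in the airway. Lavage, biopsy and foreign-body retrieval could plausibly differ in how much coughing they provoke. The covariates include pneumonia severity and a two-level baseline cough descriptor. None of them marks the child with a foreign body, although the Discussion names that condition as a source of background cough. The Discussion also says that cardiorespiratory complications vary with the type of procedure.

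At stake is the width of the confidence interval: a baseline factor that predicts the outcome can absorb residual variance without more children. A second matter is which version of the variable is meant. The article does not say whether operation type is the type scheduled or the type performed. If it is the type performed, both the existing subgroup and any added covariate would rest on something settled after study drug.

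**Working it through.** **1. The plan's own figure.** The Sample size section states: "We will require 64 subjects per group to achieve a power of 0.80 with a type I error rate of 0.05". Its inputs are a fall from 0.6 to 0.3 episodes per minute (50%) and an SD of 0.3. With n = 2(1.960 + 0.842)² × SD²/difference², these give 2 × 7.849 × 1 = 15.7, so 16 per group (17 with the t-test), not 64. The figure 64 matches a standardised difference of 0.5: 2 × 7.849/0.25 = 62.8, so 63, or 64 with the t-test. An example is a difference of 0.15 with SD 0.3. That mismatch is a separate matter. It is used here only to show power at both effects.

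**2. Precision gained, by share of variance explained.** R² is the share of outcome variance that operation type explains. The documents give no value, so it is assumed over a range. SE = 0.3 × √(1 − R²) × √(2/64), and power = Φ(difference/SE − 1.96).

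| Assumed R² | SE | Fall in SE | Power at 0.15 | Power at 0.3 |
|---|---|---|---|---|
| 0 | 0.0530 | – | 0.807 | >0.999 |
| 0.05 | 0.0517 | 2.5% | 0.827 | >0.999 |
| 0.10 | 0.0503 | 5% | 0.847 | >0.999 |
| 0.20 | 0.0474 | 11% | 0.885 | >0.999 |

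**3. Which R² fits the stated SD?** Assume shares of 60/20/20% and a within-type coefficient of variation of 0.4; neither is in the documents.

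- Assumed rates 0.65/0.75/0.90 per minute: mean 0.72; between-type variance 0.6 × 0.07² + 0.2 × 0.03² + 0.2 × 0.18² = 0.0096; within-type variance 0.16 × (0.72² + 0.0096) = 0.0845. The total is 0.0941, SD about 0.31, close to the stated 0.3. R² = 0.0096/0.0941 = 0.10. Simulated with 70 per arm, adjustment cuts the variance by about 9%, so the SE by 1 − √0.908 = 4.7%.
- Assumed rates 0.60/0.80/1.20: between-type variance 0.0544, within-type 0.1011, total SD about 0.39. The variance cut is about 35%, but the SD does not fit the stated 0.3.
- Assumed rates 0.65/0.70/0.75: variance cut about 1%.

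All three compare with an unadjusted analysis, whereas the plan already adjusts for six covariates.

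**4. Does omission do harm beyond lost precision?** Null trials were simulated (20,000 per setting, 64 per arm, total SD 0.3, linear model) with a three-level factor left out.

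| Shares; level effects per minute | R² | Mean error, unadjusted | Type I error, unadjusted | SE unadjusted → adjusted |
|---|---|---|---|---|
| 60/25/15%; 0/0.1/0.3 | 0.12 | below 0.0003 | 0.0506 | 0.0528 → 0.0500 |
| 50/30/20%; 0/0.15/0.3 | 0.15 | below 0.0003 | 0.0503 | 0.0533 → 0.0494 |

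There is no bias and no inflation.

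**5. Size of a chance imbalance.** Take a type with an assumed 20% share and a rate 0.2 per minute higher. The SD of the between-arm difference in share is √(2 × 0.2 × 0.8/64) = 0.071. Then 95% of imbalances move the estimate by at most 1.96 × 0.071 × 0.2 = 0.028 per minute. The unadjusted SE of 0.053 already includes this.

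**The case against.** The strongest reply is that nothing here is an error. Randomisation is not stratified by operation type, so no design feature obliges adjustment for it. Six covariates are already prespecified, and a seventh is a preference. A subgroup factor is not thereby shown to be prognostic. This stands, and the point is an efficiency improvement only.

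A reader might infer that chance imbalance in procedure mix distorts the result. With 70 per arm and a type making up 20% of children, a difference of at least 10 percentage points between arms has a probability of about 17%. The documents do not support that inference. Such imbalance is random error already inside the standard error and confidence interval, as steps 4 and 5 show.

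A reader might also expect a gain near 35%, or think that every secondary analysis is affected. The first needs an SD of about 0.39 against the stated 0.3. The second is too wide, because the mixed-model sentence names no covariates.

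It can also be said that the eligibility list mixes a diagnosis with procedures, so a child admitted for pneumonia has no stated operation type, and that the article does not say that manoeuvres depart from those scheduled. Both are fair. They are reasons to record the scheduled type explicitly, not evidence that the subgroup is invalid.

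Finally, extra levels could cause sparse cells in logistic models for uncommon adverse events. That stands and limits the fix.

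**Conclusion.** The point holds as a modest, cheap gain in precision. Operation type is absent from the primary model and the covariate-adjusted secondary models, although the indication is known before randomisation and the protocol itself names foreign-body irritability as a source of background cough. A scenario that fits the stated SD gives about a 9% cut in variance, or roughly 5% of the standard error, against an unadjusted analysis. On top of the existing covariates it may be less. That size rests on assumed rates and shares by type and on a linear-model approximation, and no size is claimed for the secondary endpoints. At the stated effect, power exceeds 0.999 either way, so the benefit is a narrower interval and not a rescued test.

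Omission does not bias the estimate or inflate the type I error. In logistic secondary models it also changes the odds ratio from a more conditional to a more marginal one, which is a different estimand and not confounding.

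The less sound element of the covariate list is operation time. Read as the procedure time of the endpoint sections, it is measured after randomisation, is the denominator of the primary endpoint, and is itself a secondary endpoint. Under the shared covariate list, procedure time would even be adjusted for itself. Scheduled operation type is the better measure of procedural complexity.

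**What to change.** 1. Record at the preanesthetic visit, before randomisation, the scheduled operation type in four levels: BAL; biopsy with or without BAL; foreign-body removal; other.
2. Add it as a categorical covariate to the primary model and to the models for continuous secondary endpoints, preferably in place of operation time.
3. Define the operation-type subgroup by the scheduled type, and say so.
4. In logistic models with few events, collapse levels or leave the covariate out, by a rule fixed in advance.
5. Make the change before unblinding.

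The cost is a line in the covariate list, one field recorded at the preanesthetic visit, and up to three degrees of freedom, partly offset if operation time is dropped. No more children are needed.

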## Introduction

Flexible fiberoptic bronchoscopy (FFB) maintains its critical role in pediatric pulmonology, serving indispensable diagnostic and therapeutic functions (1, 2). The guidelines of the British Thoracic Society (BTS) suggest that sedation should be recommended for all patients undergoing bronchoscopy unless there are absolute contraindications (3–5). Reducing coughing, providing a good operating environment without compromising airway patency, and maintaining adequate oxygenation are the primary goals of anesthesiologists.

The combined use of propofol and short-acting remifentanil is the most commonly used regimen during FFB (6, 7). The antitussive and analgesic properties of remifentanil may lead to a considerable reduction in coughing, thereby optimizing the working conditions for the bronchoscopist and improving patient comfort (1, 8–10). However, coughing reactions cannot be completely suppressed even when a high dosage of remifentanil is administered, and such a large dose of remifentanil is associated with more pronounced respiratory depression. The incidence of hypoxemia approaches 30% in children undergoing FFB while receiving remifentanil (1, 6, 11–14).

The technique of FFB via the laryngeal mask airway (LMA) was first introduced in 1989 and since then it has been described as a safe and convenient tool in both adult and pediatric populations (15–18). LMA with a bronchoscopy adaptor can direct the fiberscope to the glottis and provide ventilation without interfering with the maneuver of the bronchoscopist. Thus, this technology has the potential to overcome the side effects of hypoxemia during FFB, indicating that general anesthesia may be more preferable for FFB in children (15, 19–22). However, the decision of whether to use skeletal muscle relaxants remains a significant issue that anesthesiologists need to consider (23).

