### Secondary endpoints

The secondary endpoints are: (1) cumulative remifentanil dosage; (2) success rate of FFB operation; (3) hemodynamic variables; (4) cough scores in the PACU every 5 min; (5) procedure time defined as the duration from bronchoscope insertion to its removal; (6) discharge time which is defined as the interval from the removal of bronchoscopy until a modified Aldrete score of ≥9 is achieved; (7) adverse events that occur during the procedure and in the PACU, including desaturation (SpO_2_ < 90%) which is stratified into three categories: mild desaturation: 85% ≤ SpO2 < 90%, moderate desaturation: 80% ≤ SpO2 < 85%, severe desaturation: SpO2 < 80%; laryngospasma; sore throat; bradycardia or hypotension defined as a decrease of at least 20% below the age-adjusted lower limit of heart rate or arterial blood pressure; tachycardia or hypertension defined as an increase of at least 20% above the age-adjusted upper limit of heart rate or arterial blood pressure; (8) satisfaction scores of bronchoscopists during the operation; (9) satisfaction scores of anesthesiologists; (10) satisfaction scores of parents 24 h after the operation. Given the age range of our study population (1–6 years), this score is reported as a proxy measure by the child’s parent or guardian, who is present throughout the preoperative, recovery, and immediate post-discharge periods. Satisfaction scores are measured subjectively by a simple numeric score between 1 (highly dissatisfied) and 10 (highly satisfied).

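### The fully adjusted logistic model named for the secondary endpoints is unsuited to rare binary events in 140 children, and it is not ranked against the Fisher or chi-square test

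*Protocol article*

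**What the plan says.** All the analysis statements stand in the Statistical analysis section of the Protocol article.

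- **Model for secondary endpoints:** "The secondary endpoints will be analyzed using the multivariate logistic regression model or the generalized linear model, adjusting for the same covariates" as for the primary endpoint. No exception is made for endpoints with few events.
- **Covariates:** the primary analysis is described as "adjusting for the influence of covariates [the severity classification of pneumonia, BMI, age, sex and operation time, baseline cough frequency", the last in two categories.
- **General rule by data type:** "Categorical data are presented as numbers (proportions, %) and will be analyzed using Fisher’s exact test or the chi-square test".
- **Order of analyses:** for the primary endpoint, "negative binomial regression is further utilized", which suggests an unadjusted comparison followed by an adjusted one. No such wording orders the two for the secondary endpoints.
- **Multiplicity:** for adverse events, "the Benjamini-Hochberg procedure will be employed to control the false discovery rate".

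The Secondary endpoints section lists "adverse events that occur during the procedure and in the PACU, including desaturation" in three grades, laryngospasm, sore throat, and heart-rate or blood-pressure excursions at least 20% outside age-adjusted limits. It also lists the success of the procedure, which the Abstract gives as a failure rate. The section on the procedure counts a child who is given supplementary rocuronium as a failure.

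**The concern.** Some of these endpoints may occur in only a handful of the 140 children. Laryngospasm, the severe grade of desaturation and procedure failure are the obvious candidates. A logistic model with 7 or 8 slopes then has fewer events than slopes. Maximum likelihood can fail in two ways. If one arm has no event, the treatment odds ratio runs to zero or infinity. If some level of a nuisance covariate has no event, that coefficient diverges and the fit as a whole has no finite solution, even where the treatment estimate survives.

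The article's alternative wording, a generalized linear model, gives no separate route for a binary endpoint unless a different link is meant, because logistic regression is itself such a model.

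Two things are at stake. The one analysis named specifically for the secondary endpoints may give no usable estimate for some safety and failure outcomes. And each adverse event then has two available p-values, adjusted and unadjusted, while Benjamini-Hochberg takes one. If that choice is made after the fits are seen, the set of discoveries may depend on it.

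**Working it through.** The article gives no event rate, event count or power figure for the binary secondary endpoints, so there is no figure of its own to reproduce. The check asks how the stated model behaves over a range of rates.

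**Inputs from the article:** 140 children, 70 per arm; six covariates plus treatment; baseline cough in two categories.

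**Assumptions:** event rates from 1% to 30%; pneumonia severity with two or three levels (the number is not stated); illustrative covariate distributions; no dropout.

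**Step 1, slopes.** Treatment, BMI, age, sex, operation time and baseline cough take 1 each, which makes 6. Severity adds (levels − 1): 6 + 1 = 7, or 6 + 2 = 8.

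**Step 2, information.** Expected events = 140 × rate; events per slope = expected events / 7 or / 8. At 5%: 140 × 0.05 = 7, giving 7/7 = 1.0 or 7/8 = 0.88.

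**Step 3, an arm without events.** With the same rate p in both arms, P(no event in at least one arm) = 1 − (1 − (1 − p)^70)². At 2%: 0.98^70 = 0.243, and 1 − 0.757² = 0.43. At 3%: 0.97^70 = 0.119, and 1 − 0.881² = 0.22. At 5%: 0.95^70 = 0.028, and 1 − 0.972² = 0.05. In each such trial the treatment odds ratio is not finite.

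**Step 4, simulation.** There were 300 null trials per setting. A linear-programming test flagged complete or quasi-complete separation anywhere in the model, and trials with no events counted as failures. A second set of 300 trials per setting asked whether the treatment coefficient itself was non-finite. The Monte Carlo standard error near 45% is √(0.45 × 0.55 / 300) ≈ 3 percentage points.

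| Rate, both arms | Expected events | Events per slope (7 / 8) | No event in at least one arm | No finite fit (2 / 3 severity levels) | Treatment OR not finite (2 / 3 levels) |
|---|---|---|---|---|---|
| 1% | 1.4 | 0.20 / 0.18 | 74% | 95% / 99% | not run |
| 2% | 2.8 | 0.40 / 0.35 | 43% | 69% / 88% | 47% / 43% |
| 3% | 4.2 | 0.60 / 0.53 | 22% | 45% / 76% | 21% / 25% |
| 5% | 7 | 1.00 / 0.88 | 5% | 14% / 42% | 6% / 6% |
| 10% | 14 | 2.00 / 1.75 | 0.1% | 0.3% / 13% | 0% / 0.3% |
| 20% | 28 | 4.00 / 3.50 | <0.1% | 0% / 1% | not run |
| 30% | 42 | 6.00 / 5.25 | <0.1% | 0% / 0% | not run |

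The simulated loss of the treatment odds ratio stays close to the exact probability in step 3. Most of the remaining failures are therefore separation on covariates other than treatment.

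**Step 5, a treatment effect.** If rocuronium halves the control rate, the share with no finite fit is 83% / 96% at a control rate of 2%, 39% / 63% at 5%, 6% / 22% at 10% and 0% / 2% at 20%.

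Fisher's exact test can be computed whenever at least one event occurs.

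**The case against.** Four arguments can be made for leaving the text as it is.

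**The tests and the model do not conflict.** A reader might infer that the Fisher or chi-square rule contradicts the logistic model. The article does not support that. The rule is a general one for categorical data, and an unadjusted test can stand beside an adjusted model, as the wording for the primary endpoint suggests. This stands. What is missing is only the ranking.

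**A failed fit would not leave safety unanalysed.** Fisher's test is already in the plan, and 95% confidence intervals are promised for the endpoints as appropriate. This stands too. But moving to Fisher because the model failed would be a choice made after seeing the data, unless the order is fixed beforehand.

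**The rates may be higher.** The Introduction says "The incidence of hypoxemia approaches 30% in children undergoing FFB while receiving remifentanil", and the Discussion cites cardiorespiratory complications of 20% to 60%. At such rates there are 28 to 84 events, or 4 to 12 per slope with 7 slopes, and the model almost always fits. So the inference that binary secondary endpoints in general cannot be estimated is not supported. Yet these are background figures from other settings, and the Discussion also cites a laryngeal-mask series without complications. They do not settle the rate of each listed event here. Nor does the article say that each desaturation grade will have its own model.

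**Handling of sparse events belongs in the analysis plan.** That is fair for event thresholds and penalised methods, and the plan not shown may also settle the ranking. It does not remove the point, because the article does not leave the model open. It assigns a named model with a named covariate set to the secondary endpoints.

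**Conclusion.** The point holds in a limited form. For binary secondary endpoints with rates of about 5% or below, the stated model often has no finite fit, or rests on about one event per slope or fewer. The treatment odds ratio is lost in roughly 43–47% of trials at 2%, 21–25% at 3% and 5–6% at 5%. The larger figures for any failure of the fit (69–88%, 45–76%, 14–42%) should not be read as the rate at which the treatment comparison is lost, because they include separation on nuisance covariates. At 10% the treatment estimate is nearly always finite, though with only about two events per slope. At 20% or more, estimability is not a concern.

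Separately, the adjusted and unadjusted p-values are not ranked for the secondary endpoints, so the input to Benjamini-Hochberg is open.

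These conclusions rest on assumed event rates, assumed covariate distributions and two or three severity levels. They concern secondary and safety endpoints only. The change is worth making before unblinding, but it does not bear on the primary comparison.

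**What to change.** Amend the Statistical analysis section as follows.

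1. For adverse events and procedure failure, make the main analysis the unadjusted risk difference with a 95% confidence interval (a score-based interval such as Newcombe's would serve) and Fisher's exact p-value.
2. Enter only the adverse-event Fisher p-values into Benjamini-Hochberg. Keep that family as now stated, without adding procedure failure to it.
3. Keep covariate-adjusted logistic regression as a supportive analysis, only where event counts reach a threshold set in advance, with fewer covariates or with Firth's penalised likelihood. Restrict the covariates to baseline ones. Operation time is measured after randomization and appears to be the same quantity as the secondary endpoint procedure time.

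The change is wording only and needs no further children or data. Its price is less covariate adjustment for these outcomes. If Firth's method is chosen, the sponsor should check that the named software provides it.
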